## Abstract

Motor competence (MC) is defined as a global term that describes a person’s ability to be proficient in a wide range of motor acts. Based on this principle, we have created a training program that aims to determine the effect of 12 weeks of enriched athletics sports training with complementary motor activities on MC in children aged between 6 and 10 years old. The subjects will be divided into two groups: (i) the athletics training group (IG_A) that will participate in athletics training three times a week for 12 weeks, with 60 min sessions; and (ii) the athletics training + other activities group (IG_B) that will participate in athletics training twice a week and will have another activity training (gymnastics, handball, swimming, and motor games) for 12 weeks, with 60 min sessions. The two groups will be assessed at baseline and 12 weeks later. The KTK3+ will be used to assess MC. A between–within ANOVA-RM (2 [groups] × 2 [time points]) will be conducted. The results and conclusions of the implementation program will be presented in another study.

## 1. Introduction

Physical activity (PA) is widely recognized as a protective factor against a range of chronic diseases, including cardiovascular conditions, type 2 diabetes, and childhood obesity [1], and contributes to the short- and long-term improvement of the bone, muscle, and psychological health of children and adolescents [2]. Beyond its physiological benefits, PA plays a central role in the development of motor competence (MC) [1], an essential component of children’s physical literacy and a critical predictor of sustained engagement in an active lifestyle throughout life [3,4], and is related to performance in various sports [5].

MC can be defined as the ability to efficiently perform a broad repertoire of fundamental movement skills (FMSs), such as locomotor, stability, and object-control tasks [6,7]. The development of these skills is influenced by the dynamic interaction among individual (e.g., biological and hereditary), environmental (e.g., socio-cultural factors and prior experience), and task-specific factors (e.g., cognitive demand and mechanical properties) [6,8].

The evidence suggests that children with low levels of MC are more likely to show reduced PA participation, poorer physical fitness, and difficulties acquiring more complex movement skills [9,10,11]. These findings highlight the importance of early interventions, particularly during sensitive periods of motor development, when children are most responsive to motor learning through structured programs or educational strategies [12,13].

Structured interventions, such as guided motor games, quality physical education programs, and organized sports such as athletics, may be especially effective in promoting MC, as they provide diverse motor experiences and challenging FMSs. According to Lopes et al. [14], these improvements can positively affect overall physical fitness, which directly impacts cardiovascular health, body composition, and functional capacity. However, the literature lacks conclusive evidence regarding the specific effects of athletics-based programs on MC compared to multilateral or general physical education approaches [15].

Middle childhood, between the ages of 6 and 10, is a critical period for motor skill acquisition, characterized by rapid neuromuscular maturation, growth in physical capacities, and heightened adaptability to training stimuli. The evidence from school- and community-based interventions shows that structured PA (e.g., games, plyometric training, dance, and sports) or aquatics (e.g., swimming) consistently improves FMSs, coordination, and overall MC in this age group [16,17,18]. Aquatic programs have demonstrated significant gains in both global and specific motor skills, even over short durations, while land-based interventions have been shown to enhance complementary domains, such as strength, agility, and locomotor proficiency [19,20]. Collectively, the literature highlights that providing diverse, developmentally appropriate movement experiences during this sensitive growth window not only optimizes motor development but also supports long-term physical literacy and active lifestyle habits.

In this context, it becomes essential to assess the effects of systematic and structured training programs targeting MC development in early school-age children. Standardized tools, such as the Körperkoordinationstest für Kinder (KTK) [21], Test of Gross Motor Development of Ulrich [22], and Motor Assessment Batteries for Children (MABC) of Henderson and Sugden [23], have been widely used to evaluate MC due to their reliability and suitability for children aged 6 to 10 years.

Thus, the aim of this study is to design and evaluate a 12-week athletics-based training program for children aged 6 to 10, assessing its effects on MC. The hypotheses are as follows: (i) There will be significant improvement in MC after the 12-week intervention. (ii) There will be significant between-group differences in MC levels post-intervention. (iii) There will be significant improvement in MC of IG_B group after the 12-week intervention compared to the IG_A. (iv) The multi-activity program will lead to greater MC improvement in the IG_B group.

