## 2. Materials and Methods

### 2.1. Study Design

This study follows a randomized, controlled experimental design with parallel groups (1:1 allocation ratio), aimed at evaluating and comparing the effects of two types of training protocols on MC in children aged 6 to 10 years. This methodology is used considering the conclusions of the systematic review and the fact that the main researcher is an athletics coach.

The participants will be ecologically assigned into one of two intervention groups, depending upon the training schedule chosen by their parents, according to their availabilities, and being given no prior indication of which of the two programs will function on which schedule: (i) Intervention Group A (IG_A) will receive athletics-based training exclusively, three times per week for 12 consecutive weeks, with each session lasting 60 min; and (ii) Intervention Group B (IG_B) will receive a combined program consisting of athletics-based training twice per week and one additional session per week involving a complementary activity (gymnastics, handball, or motor games), also over 12 weeks and with 60 min sessions.

All the participants will undergo MC assessments at two times: (i) at baseline (T0), prior to the beginning of the intervention; and (ii) at post-intervention (T1), immediately following the 12-week training period.

The post-intervention evaluations will take place three days after the final training session, always in the afternoon, to ensure consistency in the testing conditions. Figure 1 illustrates the participant flow and intervention timeline for the trial.

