### 2.4. Instruments and Procedures

#### 2.4.1. Procedures

The intervention study was structured into several sequential phases to ensure methodological rigor and alignment with the study objectives: (i) SR—A comprehensive literature review was conducted to synthesize the current evidence on the effects of PA, organized sports, and structured training programs on MC in children; (ii) Program Design—the training protocol was developed based on the findings of the SR, incorporating best practices and evidence-based guidelines targeting fundamental motor skill development; (iii) Program Promotion—communication strategies will be employed to inform and engage the stakeholders, including the parents, coaches, and athletics club, about the program’s purpose and benefits; (iv) Definition of Procedures and Objectives—clear operational procedures and objectives for the intervention will be established to ensure fidelity in implementation and alignment with the research aims; (v) Participant Selection and Group Allocation—the sample will be defined, and the participants will be randomly assigned to either the athletics training group (IG_A) or the athletics training plus multi-activity group (IG_B); (vi) Baseline Assessment (T0)—an initial assessment will be conducted to establish the participants’ pre-intervention motor competence and anthropometric measures; (vii) Program Implementation—the 12-week training program will be administered to both intervention groups under controlled conditions; (viii) Post-Intervention Assessment (T1)—a final evaluation will be conducted 12 weeks later to assess the changes and outcomes related to the intervention; and (ix) Data Analysis and Interpretation—the collected data will be statistically analyzed to determine the effectiveness of the intervention, followed by a discussion and formulation of conclusions.

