## 4. Statistical Analysis

The required sample size was calculated using the G*Power software (3.1.9.4; Heinrich Heine University Düsseldorf, DE). As the aim is to detect differences in the KTK3+ between the two groups, and considering that the analysis will be performed on the outcomes, a between–within ANOVA-RM (2 [groups] × 2 [time points]) will be conducted, anticipating a ‘large’ effect size (f = 0.4) based on similar previous studies using the KTK3+ [26,27,36], with an α = 0.05, a statistical power of (1 − β) = 0.95, correlated dependent variables with an r = 0.50, and a violation of sphericity (ε) = 0.80. This analysis will require a total sample size of 18 individuals per group. Thus, the study should start with an additional 15% of the planned sample size for each group to account for potential dropouts as suggested by several authors (e.g., [37]). It will also be comparable to previous school-based MC studies that employed the KTK3+ as an outcome measure in early childhood and primary education contexts [24,25], considered adequate for the study objectives and the planned statistical analyses. The means and standard deviation will be calculated for all the studied variables. The normality and homoscedasticity will be verified with the Shapiro–Wilk (n < 50) and Levene’s tests, respectively. The statistical analyses will be conducted in IBM SPSS Statistics version 27. The referred to ANOVA-RM will be applied to each of the four KTK3+ battery tests independently and to the KTK3+ battery results as a whole, namely to its raw results and to its Global Motor Quotient. Thus, we will be conducting six distinct analyses and will extract conclusions from each of them, with the latter two being the most important, as global results. Nevertheless, if specificities can be found for the other four, we intend to address and to consider them.

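### Hypothesis (i), improvement after 12 weeks, can only be addressed by a time effect, which with two trained arms and no untreated group cannot show that the programme works

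*Protocol article*

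**What the plan says.** Section 1 (Introduction) states that "the aim of this study is to design and evaluate a 12-week athletics-based training program for children aged 6 to 10, assessing its effects on" motor competence. Of its four hypotheses, the first is "There will be significant improvement in MC after the 12-week intervention"; the other three compare the two groups.

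Section 2.1 describes the design as "evaluating and comparing the effects of two types of training protocols on MC in children aged 6 to 10 years". Sections 2.1 and 2.5.1 give both arms three 60-minute sessions a week for 12 weeks. Section 2.1 adds that "All the participants will undergo MC assessments at two times", before and after the programme. No untreated or waiting group and no pre-baseline control period is described. Under section 2.2 every participant is already an active member of an athletics club.

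Section 2.4.1, step (ix), says that "the collected data will be statistically analyzed to determine the effectiveness of the intervention".

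Section 4 names one inferential model, a 2 [groups] × 2 [time points] ANOVA-RM. It says "The referred to ANOVA-RM will be applied to each of the four KTK3+ battery tests independently", and also to the battery as a whole, once as raw results and once as the GMQ. The two whole-battery analyses are ranked as the most important of the six.

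**The concern.** A pre-post change in trained children has several possible causes, and the article itself supplies most of them:

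- **Maturation.** The Introduction describes this age as "characterized by rapid neuromuscular maturation, growth in physical capacities, and heightened adaptability to training stimuli".
- **Retesting.** The same battery is given twice.
- **School physical education.** Section 2.2 places these children in primary schools with structured physical education.
- **Usual training.** Participants are existing club athletes, and the Discussion presents the innovation as a change to one weekly session. This suggests that much of IG_A's programme is close to what the children would have done anyway, although their usual training is not described.

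None of these can be separated from the programme when both arms train and there are only two measurements. No later analysis plan can recover the missing comparison from these data. If a significant time effect were read as confirming hypothesis (i), and through it the aim in section 1 and the effectiveness in section 2.4.1, the trial would claim something its design cannot show. The limitations in section 5 cover scarce comparable studies, duration and intensity, and follow-up. They do not mention this.

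**Working it through.** **1. Which term addresses hypothesis (i)?** The model has three terms. The group and group-by-time terms compare the arms. Hypothesis (i) compares no arms, so only the time effect, pooled or within an arm, fits it. The article does not state this mapping; it follows by elimination.

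**2. Which outcomes are age-adjusted?**

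| Analysis in section 4 | Score type, as documented |
|---|---|
| GMQ | Normed by age and sex (section 2.4.4) |
| Raw battery total | No age adjustment stated |
| Four single tests | Not stated; section 2.4.4 gives each item a quotient, so they could be raw or normed |

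**3. The plan's own figure.** The article gives no probability for the time effect; its only related figure is 18 per group, 36 in total. From its stated inputs (f = 0.4, r = 0.50, ε = 0.80, α = 0.05, m = 2 time points, N = 36), the usual G*Power form for the within and interaction tests is λ = N·m·f²·ε/(1 − r) = 36 × 2 × 0.16 × 0.80/0.50 = 18.43, with df 0.8 and 27.2. Power is 0.989. The stated power of 0.95 needs only 27 children, or 28 with equal groups, so the figure of 36 does not reproduce. That is a separate matter; 36 is used below because the plan commits to it.

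**4. Time effect when training adds nothing.** Let every child drift by c standard deviations of the change score, from maturation, practice and usual activity combined. The time test is a t test with 34 df and noncentrality c·√36 = 6c, two-sided at 0.05. The values of c are assumptions, because the article gives no 12-week drift.

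| c | Noncentrality | P(time effect significant) |
|---|---|---|
| 0 | 0 | 5.0% |
| 0.1 | 0.6 | 9.0% |
| 0.2 | 1.2 | 21.5% |
| 0.3 | 1.8 | 41.7% |
| 0.5 | 3.0 | 83.0% |

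The SD of change is √(2(1 − r)) baseline SDs. At the plan's r = 0.50 this equals 1, so c can also be read in baseline SDs. At an assumed r = 0.80 it is √0.4 = 0.632, and drifts of 0.2, 0.3 and 0.5 baseline SD give 45.4%, 79.0% and 99.6%. With the 15% dropout allowance (18 × 1.15 = 20.7, so 21 per group) and all 42 children analysed, the figures at r = 0.50 for 0.1, 0.2, 0.3 and 0.5 are 9.7%, 24.4%, 47.5% and 88.5%.

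**5. Group-by-time effect under the same drift.** A drift shared by both arms cancels in the difference between them. In simulations of 20,000 runs per setting, with drift from 0 to 0.8 baseline SD and r of 0.50 or 0.80, this term was significant in 4.7% to 5.3% of runs. The simulated time-effect rates agreed with the table.

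**The case against.** An active-comparator trial without an untreated arm is a legitimate design, and most of the article treats it that way. Section 4 sizes the study to detect differences between the groups, and hypotheses (ii) to (iv) compare the arms. The IG_B programme description in section 2.5.1 and the Discussion state the goal as IG_B's advantage over athletics alone, and the recommendations to clubs depend on that advantage. Hypothesis (i) speaks of improvement after the programme, not because of it, and the phrase in section 2.4.1 is a generic line in a list of study phases. All of this stands, and it is why the remedy is small.

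Two features also soften the problem. The GMQ is normed by age and sex, which should remove much of the maturation on that outcome, and section 2.5 has the children familiarised with the tests beforehand, which should reduce practice gains. Neither removes it: norming does not deal with practice, school physical education or usual training, and familiarisation does not show that the remaining practice gain is zero.

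Three stronger readings are tempting but unsupported:

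- **That the time effect is the plan's stated test of the programme.** The article never says so; it is an inference.
- **That five of the six analyses use raw scores.** Only the raw battery total is clearly raw.
- **That the percentages above are error rates for this trial.** They are the power to detect an assumed drift. Read literally, hypothesis (i) would be correctly supported by a real change of any origin; the error lies in attributing that change to the programme.

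**Conclusion.** The point holds as a limit on what may be concluded. Hypothesis (i) has no comparator, only the time effect can address it, and with two trained arms measured twice that effect cannot be attributed to the programme. The wording on effects in section 1 and on effectiveness in section 2.4.1 invites that attribution, and the limitations do not warn against it.

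The size depends on a drift the article does not give. Over 0.1 to 0.5 SD of change, with 36 children, the chance of a significant time effect without any training effect runs from 9.0% to 83.0%. It should be lower for the GMQ than for the raw total if norming removes part of the drift.

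The between-arm hypotheses are not affected by drift common to both arms. They have a separate difficulty: section 2.1 lets allocation follow the schedule parents choose, while sections 2.2 and 2.4.1 call it random. This is a cheap improvement; it does not make the between-arm comparison uninformative.

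**What to change.** 1. In section 1, make hypothesis (i) descriptive: report within-arm change, chiefly in the age- and sex-normed GMQ, with 95% confidence intervals, and draw no effectiveness claim from the time effect.
2. Reword the aim in section 1 and step (ix) of section 2.4.1 to the relative effect of IG_B versus IG_A, in line with section 2.1, the IG_B programme description and the Discussion. Rest effect claims on the group-by-time term.
3. Add the lack of an untreated group to the limitations in section 5.

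The cost is wording, plus the loss of confirmatory status for one hypothesis. If the authors want to claim that the programme itself raises motor competence, they would need an untreated or waiting group, which is a change of design. None of these wording changes resolves the separate allocation problem in the IG_B versus IG_A contrast.

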## 2. Materials and Methods

### 2.1. Study Design

This study follows a randomized, controlled experimental design with parallel groups (1:1 allocation ratio), aimed at evaluating and comparing the effects of two types of training protocols on MC in children aged 6 to 10 years. This methodology is used considering the conclusions of the systematic review and the fact that the main researcher is an athletics coach.

The participants will be ecologically assigned into one of two intervention groups, depending upon the training schedule chosen by their parents, according to their availabilities, and being given no prior indication of which of the two programs will function on which schedule: (i) Intervention Group A (IG_A) will receive athletics-based training exclusively, three times per week for 12 consecutive weeks, with each session lasting 60 min; and (ii) Intervention Group B (IG_B) will receive a combined program consisting of athletics-based training twice per week and one additional session per week involving a complementary activity (gymnastics, handball, or motor games), also over 12 weeks and with 60 min sessions.

All the participants will undergo MC assessments at two times: (i) at baseline (T0), prior to the beginning of the intervention; and (ii) at post-intervention (T1), immediately following the 12-week training period.

The post-intervention evaluations will take place three days after the final training session, always in the afternoon, to ensure consistency in the testing conditions. Figure 1 illustrates the participant flow and intervention timeline for the trial.

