### 2.2. Participants

The study sample will be composed of children aged between 6 and 10 years, all of whom are to be active members of an athletics club located in the district of Leiria, Portugal. All the participants will be affiliated with the Portuguese Athletics Federation and covered by sports insurance, which includes protections regarding training sessions and data collection procedures. The selected age range fits into middle childhood, which is a critical period for motor development and the acquisition of fundamental motor skills. This age range aligns with previous research utilizing the KTK3+ battery, which has been validated and normed specifically for children within this developmental window [24,25], and was chosen because children between 6 and 10 years old are typically enrolled in primary school, where structured physical education and motor skill interventions are most effective at promoting motor competence and physical literacy [26,27]. To be eligible for inclusion in the study, the participants must meet the following criteria: (i) be aged between 6 and 10 years; (ii) be officially registered in the Portuguese Athletics Federation; and (iii) provide written informed consent signed by their legal guardians, along with the child’s verbal assent. The exclusion criteria are as follows: (i) any diagnosed physical or intellectual disability; (ii) any medical contraindications to physical exercise; (iii) failure to obtain parental consent; (iv) failure to complete the entire assessment protocol; (v) failure to complete a minimum of 80% attendance at training sessions in general and, in IG_B, failure to also complete a minimum of 80% attendance at complementary motor activities training sessions; and (vi) being outside the stipulated age range. The children meeting all the eligibility criteria will be randomly assigned to one of the two intervention groups, as described in the study design: (i) Intervention Group A (IG_A) or (ii) Intervention Group B (IG_B).

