##### Intervention Group A (IG_A) Training Program

Intervention Group A (IG_A) will participate in structured athletics training sessions three times per week, each lasting 60 min. The sessions will be held at the Municipal Stadium of Leiria—[name]—on Tuesdays and Thursdays from 17:30 to 18:30, and on Saturdays from 09:00 to 10:00. The structure of each session will follow a consistent format. (i) Warm-up (5 min): Dynamic stretching or light jogging. (ii) Main phase (45 min): Focused athletics training targeting specific objectives—technique, speed, strength, and endurance. (iii) Cool-down (5 min): Static stretching or light jogging. The participants in this group will engage exclusively in athletics training, with no additional activities. The detailed 12-week training program is presented in Table 1.

Training Components OverviewRunning and technique Training

This component focuses on enhancing the biomechanics and efficiency of running. Exercises include drills with and without equipment (e.g., cones, hurdles, pins, and ropes) to promote better posture, stride mechanics, and coordination.

Speed Training

Speed sessions emphasize velocity over short distances (10–30 m), reaction starts, and agility circuits. Activities include varied start positions (sitting, lying), slalom runs, and hurdle sprints to improve explosive acceleration and coordination.

Strength Training

Strength development will be primarily based on bodyweight resistance exercises (e.g., planks, squats, and jumping jacks) and light resistance tools (e.g., 1–2 kg medicine balls, ropes, and kettlebells). Training will follow a circuit-based format using Tabata intervals (20 s work, 10 s rest). Each session will include 4–5 rounds of 4 exercises, with 2 min rests between rounds, focusing on proper technique, functional strength, and muscular endurance.

Resistance Training

Endurance activities will be integrated through continuous running (12–15 min) and structured motor games (e.g., relays, object transport tasks, and team challenges). Given children’s limited motivation for isolated endurance drills, the activities are designed to be engaging and enjoyable, promoting a long-term affinity for aerobic exercise.

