Future research should explore the longitudinal effects, stratify the samples by the initial MC levels, and incorporate the psychosocial outcomes (e.g., perceived competence, motivation) which are known mediators of sustained engagement in PA [11,51]. Moreover, randomized controlled trials (RCTs) with matched-pair designs could provide more rigorous evidence on the causal mechanisms linking multi-activity training to motor and cognitive outcomes.

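### The protocol calls allocation randomised 1:1, but its only allocation rule is the training slot parents choose, so randomisation's protection against selection bias is not secured

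*Protocol article*

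**What the plan says.** Three places state that allocation is random.

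- Section 2.1: "This study follows a randomized, controlled experimental design with parallel groups (1:1 allocation ratio".
- Section 2.2: "The children meeting all the eligibility criteria will be randomly assigned to one of the two intervention groups, as described in the study design".
- Section 2.4.1, phase (v): "the participants will be randomly assigned to either the athletics training group (IG_A) or the athletics training plus multi-activity group (IG_B".

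The paragraph of Section 2.1 that follows the design statement gives the allocation rule: "The participants will be ecologically assigned into one of two intervention groups, depending upon the training schedule chosen by their parents". It continues: "according to their availabilities, and being given no prior indication of which of the two programs will function on which schedule".

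The training-programme sections tie each programme to one set of times. IG_A trains "on Tuesdays and Thursdays from 17:30 to 18:30, and on Saturdays from 09:00 to 10:00"; IG_B trains on the same days at the same stadium, one hour later on each day (18:30 and 10:00). Section 3 tests each group in its own training hour, IG_A at 17:30 and IG_B at 18:30.

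Section 4 plans a 2 × 2 between–within repeated-measures ANOVA on six outcomes, with no covariate named. Hypothesis (ii) in the Introduction concerns a difference between the groups in motor competence after the intervention. The limitations part of the Discussion does not mention allocation.

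**The concern.** A child's group depends on which hour suits the family. The protocol describes no chance mechanism, and a rule driven by parental availability cannot fix the group sizes at 1:1. Programme is therefore fully confounded with slot, and with whatever determines the choice of slot. What that is the protocol does not say beyond availability. A child's age, school timetable, family routine or other sports are plausible candidates, but none is documented.

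Two planned inferences are exposed. The group-by-time test compares changes, so it is biased if children in the two slots would have improved by different amounts anyway. A comparison of post-intervention levels is biased by any difference already present at T0. Either result would carry the authority of a randomised trial, and the Discussion foresees policy and curriculum recommendations if IG_B proves superior.

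**Working it through.** **Step 1: the texts side by side.** Section 2.2 does not describe a separate randomisation. It refers back to the study design, and the mechanism found there is parental choice of schedule. The three statements of random allocation therefore rest on a procedure that is not random, and no other section supplies one.

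**Step 2: does withholding the programme repair this?** It blocks one route to selection, namely parents choosing a slot because they want a programme. It leaves the route through availability open. Section 2.4.2 also promises families a full explanation of the study, methods included, at consent. The order of consent and slot choice is not stated, so how long the programme stays undisclosed is unclear.

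**Step 3: what losing 1:1 costs in power.** Inputs from Section 4: f = 0.4, α = 0.05, r = 0.50, ε = 0.80, and 18 per group (N = 36). With m = 2 time points, the noncentrality is λ = f² × N_eff × m × ε / (1 − r), where N_eff = 4·n₁·n₂/N, on 0.8 and 34 × 0.8 = 27.2 degrees of freedom.

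| Split | N_eff | Power, group-by-time test |
|---|---|---|
| 18:18 | 36.0 | 0.989 |
| 20:16 | 35.6 | 0.988 |
| 24:12 | 32.0 | 0.980 |
| 28:8 | 24.9 | 0.945 |

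Unequal groups cost little. The 18 per group is taken as stated; the same formula needs only 28 children in total for power 0.95. That is a separate matter on which this point does not depend.

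**Step 4: what bias would do.** With two groups and two times, the group-by-time test is, apart from the ε correction, a t-test on change. Assume no programme effect and a slot-related difference in change of d, in SDs of change. With 18 per group the noncentrality is d × √(18/2) = 3d on 34 degrees of freedom, and the two-sided 5% critical value is 2.03.

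| Assumed d | Noncentrality | False-positive rate |
|---|---|---|
| 0 | 0 | 0.05 |
| 0.2 | 0.6 | 0.09 |
| 0.3 | 0.9 | 0.14 |
| 0.5 | 1.5 | 0.31 |

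The values of d are assumptions; the documents give none. With r = 0.50 and equal variances, the SD of change is √(2 × (1 − 0.50)) = 1 times the SD of a single measurement. If hypothesis (ii) were tested by comparing T1 means, the same table would apply with d read as a standing gap in T1 scores.

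**The case against.** The best defence is that the two slots are on the same days, at the same stadium and one hour apart, and that parents choose without knowing the programme. Selection may then be weak. This stands as a reason not to assume a large bias. It does not make the assignment random. Even if the programmes had been placed in the slots by lot, which is not stated, that would be a single draw between two slots and not a randomisation of children.

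A second defence is that an article condenses a fuller protocol. That would excuse a missing description of sequence generation. Here the rule is given, and it contradicts the label.

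Some stronger readings are tempting but unsupported:

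- *The protocol claims freedom from selection bias.* It does not. It claims randomisation; protection from selection bias is what that label implies.
- *The Discussion admits that this is not an RCT.* It says that "randomized controlled trials (RCTs) with matched-pair designs could provide more rigorous evidence on the causal mechanisms". That can equally mean a stronger kind of RCT than this one.
- *An age gap between slots biases the main test by 0.2 to 0.25 SD.* With an assumed age SD of 1.4 years, a half-year gap and an age correlation of 0.6 to 0.7, the arithmetic is 0.5/1.4 × 0.6 to 0.7 = 0.21 to 0.25 SD. That is a baseline gap in raw scores. A constant gap cancels in the group-by-time test, and age is largely normed out of the Global Motor Quotient (Section 2.4.4). It would matter for raw post-intervention levels.
- *Losing 1:1 seriously weakens the study.* The power figures show otherwise.

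**Conclusion.** The contradiction is real and must be corrected. The protocol says randomised 1:1, while its only allocation rule is parental choice of slot, and no other section repairs this. Neither the protection that randomisation implies nor the 1:1 ratio is secured. The harm is possible bias, through differential gain in the group-by-time test and through baseline imbalance in hypothesis (ii). Its size is unknown. The false-positive rates of about 0.09 to 0.31 rest on an assumed drift of 0.2 to 0.5 SD of change, 18 children per group and no programme effect. They illustrate sensitivity and do not predict what will happen.

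**What to change.** Make the label match the procedure, in one of two ways.

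1. **Relabel.** In Sections 2.1, 2.2 and 2.4.1(v), replace *randomized*, *1:1 allocation ratio* and *randomly assigned* with *non-randomised parallel-group comparison, assignment by parent-chosen schedule with programme undisclosed*. Name this among the limitations in the Discussion and word the conclusions as non-randomised associations. Alongside the planned ANOVA-RM, add a group comparison adjusted for T0 score, age and sex. Age and sex matter mainly for the raw scores, since the quotient is already normed on them. With non-equivalent groups the adjusted and change analyses can disagree, so report both. Adjustment does not remove confounding by unmeasured factors.

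2. **Randomise.** To keep the word *randomized*, assign families who can attend either slot by a concealed, computer-generated list, and make those children the randomised analysis set.

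The first option costs wording and the RCT label. The T0 score is already measured, and age and sex are needed for the norms. The second costs one allocation list and restricts the randomised set to families flexible on time. Keeping the stated 18 per group would need 2 × 18 = 36 such children completing the study.
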